#### Causal contrast of interest

The analysis will follow an intention-to-treat approach with individuals included in the analysis according to whether they received SABR or had surgical resection at time zero, irrespective of the treatments they received subsequently. Individuals will therefore continue to contribute to the analysis until they are censored by death or the end of the 3-year follow-up period (base case) or 31 December 2023 (alternative analysis).

#### Sample size calculations

For the sample size calculations, a between-group difference in 3-year all-cause mortality of 7.5% (absolute risk scale) was defined as of clinical importance drawing on precedent observational studies and RCTs, and informed by the clinical panel. From the pilot linked registry data, the 3-year mortality rate for the eligible population who had surgical resection was 19.8%. We followed methodological recommendations for sample size calculations with IV analyses and present the required sample size under different assumptions about the proportions predicted by the IV to receive SABR versus surgery (the compliance rate).^58^
Table 4 shows that, with an assumed IV compliance rate of 0.7, the sample size that would be required to achieve power of 80% at the 5% (two-sided) level of statistical significance is 2,887 of whom at least 520 would need to be the SABR group. Based on the pilot data which included diagnoses and treatments in 2015–2018, we anticipate that in the final analysis sample for years 2015–2020, there will be at least 18 000 (3000 SABR and 15 000 surgical resection).

**Table 4 T4:** Required sample size (N) for SABR and surgical resection according to magnitude of effect size (absolute differences: SABR versus surgical resection) on 3-year mortality at 80% power, 5% level of statistical significance and assuming a ‘moderate’ level of instrument strength, corresponding to a compliance rate of 0.7

Effect size	Surgery	SABR	Total
−7.5%	2625	576	3201
−5.0%	5830	1280	7110
+5.0%	5443	1195	6638
+7.5%	2367	520	2887

SABR, stereotactic ablative radiotherapy.

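### Table 4 does not follow from the stated 19.8% surgical mortality: on the stated inputs the quoted 2,887 patients give about 70% power at +7.5%, not 80%, although the anticipated 18,000 remain ample

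*Protocol article*

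**What the plan says.** All of the material is in the protocol article, under Sample size calculations.

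- Target difference: "a between-group difference in 3-year all-cause mortality of 7.5% (absolute risk scale) was defined as of clinical importance".
- Baseline risk, from pilot registry data: "the 3-year mortality rate for the eligible population who had surgical resection was 19.8" per cent. No SABR mortality is given.
- Direction of the effect, from the Table 4 title: "absolute differences: SABR versus surgical resection) on 3-year mortality at 80% power, 5% level of statistical significance".
- With IV compliance taken as 0.7, the headline result reads: "the sample size that would be required to achieve power of 80% at the 5% (two-sided) level of statistical significance is 2,887". The SABR minimum within that total is 520.
- Table 4 totals: 3,201 (−7.5%), 7,110 (−5%), 6,638 (+5%) and 2,887 (+7.5%).
- Anticipated analysis sample for 2015–2020: at least 18,000, made up of 3,000 SABR and 15,000 surgery.

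**The concern.** If surgery carries 19.8% mortality and the effect is SABR minus surgery, positive rows put SABR at 24.8% or 27.3%, and negative rows at 14.8% or 12.3%. Binomial variance rises as the risk moves towards 50%, and the smaller SABR arm contributes most of the variance of the difference. A positive effect should therefore need more patients than a negative effect of the same size. Table 4 shows the opposite: 2,887 is below 3,201, and 6,638 is below 7,110.

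This is the only sample size justification given for the primary outcome. At stake is whether the printed sizes, and the power claimed for the row singled out in the text, follow from the inputs printed beside them.

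**Working it through.** **Inputs.** From the text and Table 4: 19.8%; effects d of ±5 and ±7.5 percentage points; 80% power; two-sided 5%; compliance 0.7. The allocation is not stated as an input. It is read off the table: 520/2,887 = 18.0% SABR, and the other three rows also give 18.0%, so r = 82/18 = 4.556 surgical patients per SABR patient.

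**Formula** (unpooled two-proportion, effect diluted by compliance):

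n_SABR = (1.960 + 0.842)² × [p_surg(1 − p_surg)/r + p_SABR(1 − p_SABR)] / (0.7² × d²), and n_surg = r × n_SABR. Here (1.960 + 0.842)² is 7.849 with unrounded normal quantiles.

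**Step 1: reproduce the printed table.** Put p_SABR = 0.198 and p_surg = 0.198 − d.

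Example at +7.5%: p_surg = 0.123, so the bracket is 0.1079/4.556 + 0.1588 = 0.1825. Then n_SABR = 7.849 × 0.1825 / (0.49 × 0.005625) = 519.6.

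| Effect | Surgery rate | SABR n (printed) | Surgery n (printed) |
|---|---|---|---|
| −7.5% | 27.3% | 576.3 (576) | 2625.2 (2625) |
| −5% | 24.8% | 1279.7 (1280) | 5830.0 (5830) |
| +5% | 14.8% | 1194.8 (1195) | 5443.0 (5443) |
| +7.5% | 12.3% | 519.6 (520) | 2367.2 (2367) |

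All eight cells agree to the nearest patient.

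**Step 2: use the inputs as stated.** Put p_surg = 0.198 and p_SABR = 0.198 + d.

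Example at +7.5%: p_SABR = 0.273, so the bracket is 0.1588/4.556 + 0.1985 = 0.2333. Then n_SABR = 664.4, rounded up to 665, with 3,027 surgical patients.

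| Effect | SABR rate | SABR + surgery | Total | Printed | Power at printed size |
|---|---|---|---|---|---|
| −7.5% | 12.3% | 407 + 1,852 | 2,259 | 3,201 | 91.5% |
| −5% | 14.8% | 1,032 + 4,698 | 5,730 | 7,110 | 87.7% |
| +5% | 24.8% | 1,419 + 6,461 | 7,880 | 6,638 | 73.0% |
| +7.5% | 27.3% | 665 + 3,027 | 3,692 | 2,887 | 69.8% |

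Power in the last row: the standard error is √(0.1588/2367 + 0.1985/520) = 0.02118. Then 0.7 × 0.075/0.02118 = 2.478, and Φ(2.478 − 1.960) = 0.698.

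**Step 3: try other formulas with 19.8% in surgery.** Totals in the order −7.5, −5, +5, +7.5:

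- pooled: 2,704 / 6,370 / 7,350 / 3,359
- continuity-corrected: 2,884 / 6,643 / 7,623 / 3,537
- arcsine: 2,567 / 6,181 / 7,500 / 3,454
- pooled with the SABR rate diluted to 19.8% + 0.7d: 2,819 / 6,534 / 7,219 / 3,274

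None gives the printed 3,201 / 7,110 / 6,638 / 2,887. Power at 2,887 for +7.5% is 74.2% (pooled), 75.1% (diluted, pooled) and 71.8% (diluted, unpooled).

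**Step 4: reverse the sign label.** The unpooled totals become 3,692 / 7,880 / 5,730 / 2,259, which do not match. The nearest candidate with 19.8% in surgery is the diluted pooled version with the sign reversed: 3,277 / 7,219 / 6,534 / 2,817. It misses the rows by 2.4%, 1.5%, 1.6% and 2.4%, and it contradicts the table's own direction.

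**Step 5: the anticipated sample.** With 15,000 surgical and 3,000 SABR patients, surgery at 19.8% and compliance 0.7, power is over 99.9% (−7.5%), 99.8% (−5%), 98.4% (+5%) and over 99.9% (+7.5%). For +5%, the standard error is √(0.1588/15000 + 0.1865/3000) = 0.00853, 0.7 × 0.05/0.00853 = 4.10, and Φ(4.10 − 1.96) = 0.984.

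**The case against.** The strongest reply is that nothing in the study turns on these figures. The diagnoses fall in 2015–2020 and have already been made, so Table 4 sets no recruitment target, stopping point or data cut. The corrected 3,692 is about one fifth of 18,000. With the anticipated sample, 80% power holds down to a compliance of about 0.33 at +7.5% (2.802 × 0.00876/0.075) and about 0.48 at +5% (2.802 × 0.00853/0.05). This stands, and it limits how serious the point is. A reader who sees 70% power might infer that the study is underpowered; the protocol's own anticipated numbers rule that out.

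The second reply is that the cause is inferred. The article prints no SABR mortality, allocation or formula and refers to a methods source for the calculation. The 18:82 split was itself read off the table. A reader might take it as established that the authors put 19.8% in the wrong arm. The documents do not say so, and the slip could lie in the prose or, less plausibly given the imperfect fit, in the sign label. This also stands, and for that reason the remedy has to leave more than one route open.

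Neither reply removes the contradiction. Under every formula tried, the stated baseline, the stated direction and the printed sizes do not agree, and nothing elsewhere in the article reconciles them.

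**Conclusion.** The stated sample sizes and the stated inputs are inconsistent, and the figures should be corrected. Taking the text at its word (surgery 19.8%, effect SABR minus surgery), the printed totals are about 42% and 24% too large for −7.5% and −5%, and about 16% and 22% too small for +5% and +7.5%. The row quoted in the text is on the unfavourable side: it needs 28% more patients (3,692/2,887 = 1.28), and as printed it has 69.8% power under the formula that generates the table, or 72–75% under the other versions tried.

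These sizes assume compliance 0.7 and the table's 18:82 split. That 19.8% was used as the SABR rate is a strong inference from eight matching cells, not a documented fact. The point concerns published figures only: design, analysis and the adequacy of the anticipated sample are unaffected. If the prose is the slip, Table 4 stands as printed, and its largest total, 7,110 with 1,280 SABR, is also well within 18,000 with 3,000 SABR.

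**What to change.** First establish from the source calculation which group the 19.8% describes. Then do one of the following:

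- If it is the surgical rate, as the text says, recompute Table 4 with surgery at 19.8% and SABR at 19.8% plus the effect. Under the table's formula this gives 2,259, 5,730, 7,880 and 3,692. Change the headline sentence to 3,692 in total, of whom at least 665 SABR, at +7.5%.
- If it is the SABR rate, keep Table 4 and correct the sentence that attributes 19.8% to surgery.

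If the source calculation shows that the sign was reversed instead, correct the effect labels and check the rows again. In every case, print the mortality assumed in each arm, ideally with the allocation and formula, so that a reader can reproduce the table.

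The cost is one table and one or two sentences, with no change to data, design or analysis. If the table is recomputed, the positive rows become less favourable and the negative rows more favourable.

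### Table 4 does not match its stated 19.8% surgical mortality: for a +7.5% effect the quoted 2,887 gives about 67–70% power, not 80%

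*Protocol article*

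**What the plan says.** All of this is in the protocol article, Sample size calculations, including Table 4.

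- **Target difference:** "a between-group difference in 3-year all-cause mortality of 7.5% (absolute risk scale) was defined as of clinical importance". No direction is given.
- **Baseline:** from the pilot data, "the 3-year mortality rate for the eligible population who had surgical resection was 19.8" per cent.
- **Sign convention:** the Table 4 caption describes the effects as "absolute differences: SABR versus surgical resection) on 3-year mortality at 80% power". A positive effect therefore means higher mortality with SABR.
- **Requirement in the text:** "with an assumed IV compliance rate of 0.7", the number needed "to achieve power of 80% at the 5% (two-sided) level of statistical significance is 2,887". The sentence then sets a minimum for one group: "of whom at least 520 would need to be the SABR group". This is the plus row of the table, "7.5% 2367 520 2887" (effect, surgery, SABR, total).
- **Other rows (surgery / SABR / total):** −7.5% is 2,625 / 576 / 3,201; −5% is 5,830 / 1,280 / 7,110; +5% is 5,443 / 1,195 / 6,638.
- **Expected sample:** "there will be at least 18 000 (3000 SABR and 15 000 surgical resection".

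**The concern.** The order of the rows conflicts with the stated inputs. With surgery at 19.8%, +7.5% puts SABR at 27.3% and −7.5% puts it at 12.3%. The binomial variance p(1−p) is 0.1985 at 27.3% and 0.1079 at 12.3%. SABR is the smaller group, so its variance carries most of the weight. For the same absolute difference the plus row must need more patients, and the same holds for 5% (SABR 24.8% against 14.8%). Table 4 has the minus rows larger in both pairs.

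At stake is the sample size and power stated for the primary outcome. A reader who takes the plus rows as the numbers needed to detect excess mortality with SABR, for example when judging how much a smaller subgroup can show, would use requirements that are too low.

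**Working it through.** **Inputs.** Surgical mortality 19.8%, compliance c = 0.7, two-sided 5%, 80% power and effects of ±5% and ±7.5% are all stated. The SABR share in Table 4 follows from its rows: 520/2,887, 576/3,201, 1,195/6,638 and 1,280/7,110 are each 18.0%. The anticipated share is 3,000/18,000 = 16.7%, or 1:5.

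**Formula (unpooled two proportions, inflated for compliance).** With SABR share s, surgical risk p_S, SABR risk p_R and difference d:

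V = p_S(1−p_S)/(1−s) + p_R(1−p_R)/s

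N = (1.960 + 0.842)² × V / (c² d²) = 7.849 × V / (0.49 d²)

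**Step 1: reproduce Table 4.** Set s = 0.18, put 19.8% in the SABR arm, and take surgery as 19.8% minus the effect.

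| Effect | Surgery risk | SABR risk | V | N computed | N in Table 4 |
|---|---|---|---|---|---|
| −7.5% | 27.3% | 19.8% | 1.1242 | 3,201.5 | 3,201 |
| −5% | 24.8% | 19.8% | 1.1096 | 7,109.7 | 7,110 |
| +5% | 14.8% | 19.8% | 1.0360 | 6,637.8 | 6,638 |
| +7.5% | 12.3% | 19.8% | 1.0138 | 2,886.8 | 2,887 |

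All four rows agree to rounding.

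**Step 2: the stated baseline, same formula.** Put 19.8% in the surgical arm and take SABR as 19.8% plus the effect.

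| Effect | SABR risk | N (SABR) at 18% | N (SABR) at 1:5 |
|---|---|---|---|
| −7.5% | 12.3% | 2,258 (406) | 2,386 (398) |
| −5% | 14.8% | 5,729 (1,031) | 6,069 (1,011) |
| +5% | 24.8% | 7,879 (1,418) | 8,390 (1,398) |
| +7.5% | 27.3% | 3,691 (664) | 3,934 (656) |

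For +7.5% at 1:5: V = 0.1588/0.8333 + 0.1985/0.1667 = 1.3814, and N = 7.849 × 1.3814 / (0.49 × 0.005625) = 3,934.

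**Step 3: other formulas with 19.8% in surgery, +7.5%, 18% share.** Pooled variance gives 3,356, continuity-corrected 3,538, and compliance applied as dilution of the effect 3,276 to 3,522. All exceed 2,887.

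**Step 4: power of the quoted 2,887.** z = 0.075 × 0.7 / √(V/2,887) = 0.0525 / √(V/2,887), and power = Φ(z − 1.960).

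- +7.5%, 18% share: V = 1.2963, z = 2.478, power 70%.
- +7.5%, 1:5: V = 1.3814, z = 2.400, power 67%.
- −7.5%, 18% share: V = 0.7929, z = 3.168, power 89%.
- −7.5%, 1:5: V = 0.8378, z = 3.082, power 87%.

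**Step 5: the anticipated sample, 3,000 SABR and 15,000 surgery, 19.8% in surgery.** Power exceeds 99.9% for 7.5% in either direction. For 5% it is 99.8% (−5%) and 98.4% (+5%).

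**The case against.** The arm placement is inferred. The article prints no formula and relies on a cited method that is not at hand. Reversed sign labels are a possible rival explanation: with 19.8% in surgery, the signs swapped and a simple pooled variance, the rows come within about 0.6% of the table, though not to rounding. That does not rescue the table, because on either account the printed rows contradict the stated baseline and sign convention. The ordering argument needs no exact formula.

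The stronger objection is that nothing in the study turns on 2,887. The cohort is fixed by diagnosis years, and 18,000 is more than four times 3,934 and more than twice the largest corrected row, 8,390. This stands, and it limits the weight of the point.

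A reader might draw three further inferences that the documents do not support:

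- **That the text picked the easier 7.5% row.** On the printed table, 2,887 is below 3,201. Both rows are shown with their signs, however, and once 19.8% is in the surgical arm, +7.5% is the more demanding direction.
- **That an 18% share contradicts 16.7%.** The expected counts are rounded minimums, not a planned allocation. The difference moves N by only 6–7%.
- **That 2,887 falls short in both directions.** With the stated baseline it gives 87–89% power for −7.5%.

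**Conclusion.** The point holds as an error in the stated sample size. Table 4 is inconsistent with its own baseline and sign convention. The best-fitting explanation is that 19.8% was used as the SABR rate. For +7.5% the requirement is 3,691 at an 18% share or 3,934 at 1:5, so 2,887 is low by 22% or 27%, and its power is about 70% or 67% where 80% is stated. The +5% row is understated too, and both minus rows are overstated.

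These sizes assume the unpooled formula, which is the one that reproduces the table, and compliance of 0.7. It would be wrong to conclude that the study is underpowered: on these assumptions the anticipated 18,000 is sufficient for every effect in the table.

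**What to change.** Recompute Table 4 with 19.8% in the surgical arm, preferably at the anticipated 1:5 split. With the table's own formula the totals become 2,386 (−7.5%), 6,069 (−5%), 8,390 (+5%) and 3,934 (+7.5%). In the text, name the direction of the effect and quote the more demanding 7.5% row, about 3,934 of whom 656 SABR. State the formula and the SABR share with the table. Replacing 2,887 by the printed 3,201 would not be a correction, because that row carries the same fault.

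The cost is one restated table and one sentence, which could be posted through the study's published route for protocol deviations. The stated requirement becomes less favourable. No extra patients are needed and the design and analysis do not change.

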### Cost-effectiveness analysis

#### Overview

We will assess the comparative cost-effectiveness of SABR versus surgical resection for individuals with early-stage NSCLC. The CEA will take a hospital perspective and report costs, outcomes and cost-effectiveness over a 3-year time horizon. This perspective and time horizon are anticipated to be sufficient to capture the important differences in mean costs and mean outcomes between the comparison groups. The CEA will incorporate individual-level resource use and mortality data from the linked NDRS data, combined with unit costs and health-related quality of life (HRQoL) estimates from the literature.^59^,^61^ The CEA will follow the assessment of comparative effectiveness in using IV methods to reduce the risk of residual confounding. We will report the net health benefits^62^ of SABR with curative intent versus surgical resection overall and for the subgroups of interest described in the Main analyses section.

#### Resource use and unit costs

From the linked NDRS data, we will identify resource use for those categories anticipated to drive incremental costs, including the delivery of SABR, surgical procedures, hospital inpatient stays (including all readmissions, subsequent surgery, palliative care), outpatient visits, diagnostic procedures and subsequent treatment (eg, systemic therapies, radiotherapy or salvage surgeries). We will extract data on the receipt of SABR as well as the Office of Population Censuses and Surveys Classification of Interventions and Procedures codes of all surgical resections and operative procedures performed on each eligible patient. For hospital inpatient stays, we will distinguish between the time spent in critical care and on general wards.

Unit costs, including those for SABR and surgical strategies, will be taken from the NHS Cost Collection^63^ and the Personal Social Services Research Unit Cost databases.^64^ We will combine resource use with unit costs to report total costs per patient over 3 years (see also the Alternative analyses section).

#### Outcomes for the CEA

We will calculate the number of life years from the date of treatment start up to 3 years (base case) and for the maximum observation period available (alternative analyses). The NRDS linked data will be used to identify cancer recurrence and disease progression based on diagnoses and procedures captured in subsequent hospital admissions, registration of new tumours and treatment receipt, including surgery, chemo-oncology, immuno-oncology therapy and radiotherapy using a novel approach developed for bowel cancer.^65^ The IV analysis will compare the adjusted proportions of cancer recurrences, common severe adverse events (eg, pneumonia, respiratory distress syndrome or failure and myocardial infarction)^66^ following SABR versus surgical resection. Pending these results, we will apply appropriate HRQoL estimates from the literature.^59^,^61^ For individuals who died of lung cancer, lower HRQoL will be assigned in the six months prior to death.

We will combine survival time with appropriate HRQoL estimates from the literature and use the ‘area under the curve’ approach^67^ to report quality adjusted life years (QALYs) at 3 years from treatment start. We will calculate the incremental net benefit by valuing the incremental QALYs (difference in mean QALYs for SABR vs surgical resection) with alternative threshold levels for cost per QALY gain, including those specified by NICE (eg, £20 000 and £30 000).

### Planned statistical analyses

#### Main analyses (base case)

For the main analysis (base case) we will use an IV to reduce the risk of confounding that is due to unmeasured baseline variables, such as tumour location, as well as measured confounders, such as age or cancer stage.^58^ The IV will exploit natural variation across the cancer networks and over time in the proportion of eligible individuals who had SABR rather than surgical resection (see figure 2). This natural variation implies that people with a similar prognosis at baseline will differ in whether they receive SABR or have surgical resection simply according to the cancer network or the time period in which they have treatment. The definition of cancer referral networks aligns with the ‘hub’ and ‘spoke’ model of care for lung cancer^68^ and comprises a surgical centre (the hub) with a multidisciplinary team who inform the decision of SABR versus surgical resection and the surrounding hospitals (the spokes) that refer individuals with NSCLC to the centre. The IV is the historic proportion of eligible individuals with NSCLC within each cancer referral network who had SABR versus surgical resection. This proportion is calculated for each individual for the six months before that individual starts either treatment.

**Figure 2 F2:**
[figure not shown]
The proportion of eligible patients in each cancer referral network who had SABR with curative intent versus surgery in the NDRS pilot data (2015–2018). NDRS, National Disease Registration Service; SABR, stereotactic ablative radiotherapy.

A valid instrument must meet three main conditions.^58^ First, the instrument must predict the treatment received, which can be formally assessed.^69 70^ For the instrument to be of sufficient strength, the F-statistic summarising the association between the IV and the treatment received must exceed 100.^71^ In the NDRS pilot data, the corresponding F-statistic^70^ was 329. Second, the instrument must be independent of baseline covariates which are prognostic of the outcome of interest. This can be evaluated for the observed baseline measures. We found that the observed baseline variables were balanced across different levels of the instrument (figure 3). Third, the instrument must only have an effect on the outcomes through the treatment received, which cannot be evaluated empirically. If there were imbalances in measured covariates across levels of the IV this would raise concerns about the second and third IV assumptions. We will address this potential risk of confounding by adjusting for any residual differences in measured contextual and temporal confounders in the second stage (outcome) regression. These differences may pertain to variations in the quality of cancer care provided across the networks. By adjusting for these variables, we can make a weaker assumption that the IV, the proportion in the network who received SABR, does not have a direct effect on the outcome *after* adjusting for any differences in contextual variables pertaining to the quality of care and the time period.

